## Abstract

**Introduction:**

Type 2 diabetes mellitus (T2DM) and obesity are pandemic diseases that lead to a great deal of morbidity and mortality. The most effective treatment for obesity and T2DM is bariatric or metabolic surgery; it can lead to long-term diabetes remission with 4 in 10 of those undergoing surgery having normal blood glucose on no medication 1 year postoperatively. However, surgery carries risks and, additionally, due to resource limitations, there is a restricted number of patients who can access this treatment. Moreover, not all those who undertake surgery respond equally well metabolically. The objective of the current research is to prospectively investigate predictors of T2DM response following metabolic surgery, including those directly involved in its aetiopathogenesis such as fat distribution and genetic variants. This will inform development of a clinically applicable model to help prioritise this therapy to those predicted to have remission.

**Methods and analysis:**

A prospective multicentre observational cohort study of adult patients with T2DM and obesity undergoing Roux-en-Y gastric bypass surgery. Patients will be comprehensively assessed before surgery to determine their clinical, metabolic, psychological, genetic and fat distribution profiles. A multivariate logistic regression model will be used to assess the value of the factors derived from the preoperative assessment in terms of prediction of diabetes remission.

**Ethics and dissemination:**

Formal ethics review was undertaken with a favourable opinion (UK HRA RES reference number 18/LO/0931). The dissemination plan is to present the results at conferences, in peer-reviewed journals as well as to lay media and to patient organisations.

**Trial registration details:**

ClinicalTrials.gov, Identifier: NCT03842475.

Strengths and limitations of this studyOne of the first studies to prospectively and comprehensively profile patients with type 2 diabetes mellitus
(T2DM) undergoing bariatric surgery to assess predictors of diabetes remission.Collects prospective data on factors known to be involved in the aetiopathogenesis of T2DM such as genetics and fat distribution.A biorepository of tissue samples will be collected to allow multi-omics analysis.Long-term follow-up for up to 10 years will enable assessment of the durability of remission.The primary limitation is that this is a preliminary study; it will identify and internally validate predictors and will require further external validation in other cohorts.

## Introduction

Currently the majority of adults globally are obese or overweight. The increasing number of those with obesity is closely mirrored by the increasing prevalence of diabetes; at present over 400 million adults are estimated to be affected, 90% of whom have type 2 diabetes mellitus (T2DM).^1^ The close relationship between obesity, particularly ‘central’ or abdominal obesity, and T2DM has now been shown in multiple studies.^2 3^ Obesity, as defined by ethnicity-specific body mass index (BMI) cut-offs, is the principal modifiable risk factor for developing T2DM. However, the weight threshold at which T2DM develops varies between individuals, with significant variation among different ethnicities exemplifying two of the important factors that are thought to influence risk: the individual pattern of where fat is deposited in the body and underlying genetic predisposition.^4–9^

Epidemiological studies have shown those with a higher waist:hip ratio (WHR), representing centrally-deposited fat, are more likely to develop the disease.^3^ Central fat or higher intra-abdominal visceral fat deposition is known to be metabolically more damaging with increased likelihood of developing abnormalities in glycaemia, blood pressure and lipid profiles.^10^ However, it is not simply central adiposity but also ectopic fat that may have pathophysiological consequences.^11^ Evidence is accumulating regarding the detrimental effect on glycaemia from fat ectopically deposited within liver, skeletal muscle and pancreas.^12^

T2DM shows heritability and many pathogenic variants have been discovered which influence β cell functioning and insulin resistance.^13 14^ Moreover, genetic susceptibility to T2DM is known to be correlated with phenotypic changes in fat distribution: genetic variants associated with insulin resistance have been found to be correlated with lower subcutaneous adipose tissue (SAT) and a genetic predisposition to diabetes has been found in those with impaired SAT adipogenesis and increased waist circumference.^15^ Combining GWAS (genome-wide association study) data to derive personalised genetic risk, while challenging, has been successfully achieved in other conditions with the potential to add further precision to a predictive score.^16 17^

### Remission of diabetes

The most effective treatment for obesity and diabetes is bariatric surgery; this has been relabelled as ‘metabolic surgery’ to highlight its primary utility as a therapy for diabetes and other related metabolic dysfunctions, including dyslipidaemia and non-alcoholic fatty liver disease, as opposed to primarily treating excess weight.^18^ Randomised control trials have shown metabolic surgery consistently outperforms best medical therapy in improving glycaemic control and leads to durable remission in a significant proportion.^19 20^ Roux-en-Y gastric bypass (RYGB), the gold-standard procedure for those with diabetes, involves the construction and anastomosis of a small pouch of stomach to jejunum such that food is diverted to the jejunum, bypassing the majority of the stomach and the duodenum. Following RYGB, remission of diabetes (as defined by markers of normoglycaemia in the absence of anti-diabetic medication) occurs in 4 in 10 patients at 1 year and this remission is long-lasting: the majority of these patients remain in remission at 5 years.^18–20^ Furthermore, surgery also leads to a reduction in microvascular and macrovascular complications associated with diabetes.^21^

No single unifying mechanism found thus far can explain the improvement in glycaemic control seen in those with T2DM following RYGB. While it is clear that the 25% to 30% weight loss seen by 12 to 18 months postoperatively plays a significant role, improvement in glycaemia occurs within days following surgery, prior to any significant weight reduction, suggesting a role for weight-loss independent mechanisms.^22^ Reduced calorie intake post-surgery is one such putative weight-loss independent mechanism for the immediate improvement in glycaemia as those on a very low-calorie diet can achieve reversal of the metabolic features of diabetes.^23^ However, caloric restriction normally also leads to hom-eostatic compensation or counter-regulation including increased appetite, reduced energy expenditure and secretion of orexigenic gut hormones. In contrast, following surgery, appetite is known to reduce and weight-adjusted resting energy expenditure may increase.^24–26^

It is likely that caloric restriction and weight loss are only two of the many mechanisms that contribute to the postoperative metabolic improvement seen. Insulinotropic and anorexigenic gut hormones including glucagon-like peptide 1 (GLP-1), peptide YY (PYY) and oxyntomodulin increase following surgery.^27 28^ PYY and GLP-1 have been implicated in the restoration of insulin secretion after RYGB.^29 30^ Furthermore, infusion of such hormones leads to improved metabolic control.^31^ Changes in their secretion have been correlated with postoperative metabolic and weight loss response.^30 32 33^ Associated with these findings are the increased levels of plasma bile acids after surgery which have been correlated with increased levels of GLP-1.^34^ Bile acids have been implicated in the improvement in glycaemia via signalling through the nuclear farnesoid X receptor and G-protein-coupled GPBAR1/TGR5 receptor.^35 36^ GPBAR1/TGR5 activation leads to increased secretion of insulinotropic GLP-1 and modulates insulin sensitivity in tissues such as muscle and brown adipose tissue.^37^ While changes in bile acids play a role in metabolic improvement, this still remains an area of active research.

Further adding to the complexity of the mechanism of remission, differences in the gut microbiota, that is, the microorganisms commensal within the gut, have been seen between lean and obese individuals.^38^ There is some evidence that, as a regulator of the host’s metabolism, the gut microbiota may be associated with obesity through several mechanisms such as enhancement of fat storage.^39^ Significant changes occur in the gut microbiota following surgery^40^ but the causal relationship between the microbiotal changes and metabolic improvements, that is, whether the metabolic improvements come from the microbiotal changes or vice versa, has yet to be established. Furthermore, there is a bi-directional relationship between the microbiome and bile acids: while the gut microbiota have a role in converting primary to secondary bile acids, bile acids can affect the diversity of gut microbiota.^41^

We conclude that to further explore the mechanisms of remission after metabolic surgery a comprehensive multi-omics approach must therefore be employed.

### Predicting diabetes remission following surgery

There is a substantial disparity between the numbers eligible for metabolic surgery and the resources available to deliver it; in the UK 2 million people fulfil the criteria but surgery is only being performed in 5600 patients per year.^42^ Furthermore, there is variation in the metabolic response between individuals such that less than half are expected to have complete diabetes remission at 1 year following surgery. If we can better predict who will benefit from surgery by remission of diabetes we can better inform patients and direct the surgery to where it will be most effective.^43^ Currently in the UK, BMI cut-offs dictate eligibility for surgery, along with more recently introduced diabetes duration and ethnicity criteria.^44^ However, baseline BMI does not correlate well with the likelihood of diabetes remission thus other predictors are necessary to better inform eligibility based on intended benefit.^45^

Predictive factors have been found in multiple, mainly retrospective studies and some have been incorporated into models of diabetes remission.^46–48^ These models have tried to predict diabetes remission based on easily available clinical data making them translatable to everyday practice. However, they remain limited in their clinical applicability.^49^ Moreover, none have incorporated fat distribution or genetic risk factors which have important aetiopathological roles in T2DM. Furthermore, they are, in most cases, based on retrospective studies. One problem faced in this instance is that the consensus definition of diabetes remission depends on withdrawal of pharmacological therapies for T2DM for 1 year. There is often no standardised pathway to assess the remission status after surgery, which can lead to differing practice among clinicians thus hampering the ability to define remission status with accuracy.

This study will use genetic profiling, identifying genetic variants associated with fat distribution patterns, β-cell dysfunction, T2DM or insulin resistance, combined into an individual genetic-risk score for each patient.^50 51^ Moreover, it will assess the distribution pattern of total body fat and markers of ectopic fat deposition within the liver, muscle and pancreas. These variables will be tested to assess if they are predictive of diabetes remission. In addition, patients will be profiled for variation in biomarkers postulated to be mechanistically involved in diabetes remission including gut hormones, microbiotal changes and bile acids.

The ultimate aim of the study will be to identify novel covariates predictive of diabetes remission after metabolic surgery, with the intention that these can be further investigated for their predictive power in larger studies and other populations.

## Objectives

### Primary objective

To develop and internally validate a predictive model of diabetes remission following metabolic surgery.

### Secondary objectives

To assess changes in diabetes and obesity-related comorbidities following surgery and investigate the mechanisms of diabetes remission.

## Methods and analysis

This is a prospective, multicentre observational cohort study investigating predictors of diabetes remission in patients with diabetes/pre-diabetes undergoing RYGB surgery with standardised biliopancreatic and alimentary limb lengths of 50 cm and 100 cm, respectively.

### Participants and selection criteria

Study participants will be recruited according to the inclusion and exclusion criteria detailed in table 1.

**Table 1 T1:** Inclusion and exclusion criteria

Inclusion criteria	Patients with pre-diabetes or diabetes eligible for bariatric/metabolic surgery on the NHS, that is, BMI ≥35 with a comorbidity or ≥40, lower BMIs accepted if of Asian origin or recent-onset diabetes, referred to Imperial Weight Centre or Chelsea and Westminster NHS Trust^44 55^
	Stable weight (≤10% variation) for at least 3 months
Exclusion criteria	Current pregnancy
	Inability to give informed consent
	Type 1 diabetes, low fasting C-peptide, secondary diabetes or absence of β-cell function
	Unable to undergo DEXA
	Cirrhosis, ascites or other condition that may modify body fat composition, for example, underlying malignancy
	Participation in a concurrent/recent interventional trial within the last 3 months that would affect the current study results or mean that undergoing the study would be too burdensome for the participant
	Unable to understand English

BMI, body mass index; DEXA, dual-energy X-ray absorptiometry; NHS, National Health Service.

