### Outcomes

The primary outcome is diabetes remission (partial and complete) or diabetes remission (complete) measured postoperatively at 15 months. This will be defined by American Diabetes Association criteria, such that complete remission is fasting glucose <5.6 mmol/L, glycated haemoglobin (HbA1c) <42 mmol/mol on no anti-diabetic agents, and partial remission is defined as fasting glucose 5.6–6.9 mmol/L, HbA1c <48 mmol/mol on no anti-diabetic agents. Patients will be seen at 3 months as part of routine clinical follow-up and will have anti-diabetic medication stopped according to a standardised pathway. An assessment of diabetes remission will also be made at 1, 2, 3 and 5 years.

In addition to the primary outcome we will collect phenotyping data to allow assessment of diabetes severity and obesity associated comorbidities.

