### Sample size calculation

Using a logistic regression model to predict a 75% partial and completed diabetes remission rate from multiple predictors, a sample size of 150 provides 90% power at the two-sided 5% significance level to detect an OR of 2.0 per SD of any continuous predictor.^52^ This allows for up to 10% of the variation in any one predictor to be explained by the others in the model, and 15% loss to follow-up. The area under the receiver operating characteristic (ROC) curve, overall performance measure, will be estimated with a 95% CI width of at most±0.1 for an area above 0.65. With data analysed from 100 patients there would still be in excess of 80% power to detect the OR of 2.0, and a precision of at most±0.12 for the ROC curve area. This is reasonable enough to allow some deviation in assumptions, such as the dropout rate.

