DPP-IV, Dipeptidyl peptidase-IV; FIB-4, Fibrosis-4 score; GLP-1, Glucagon-like peptide 1; HOMA, Homeostatic model assessment; MRI, magnetic resonance imaging; NAFLD, Non-alcoholic fatty liver disease; SGLT-2, sodium-glucose co-transporter-2; TCI-R, Temperament and Character Inventory-Revised.

A logistic regression model predicting diabetes remission assessed at the 15 months visit will be built using the prospective cohort data. This was chosen in preference to an ordinal regression approach, such as the proportional odds model, because of the need to have a clear and independent interpretation of the predictive contribution both to complete remission and to complete and partial remission. Logistic regression was preferred over another alternative approach, discriminant analysis, for the same reason and because logistic regression provides predicted probabilities for individual patients which can then be used within ROC curve analysis to provide estimates of sensitivity and specificity of the regression models measuring their accuracy to predict the diabetes remission outcome of metabolic surgery.

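### Pre-diabetic patients are eligible and the text does not keep them out of the remission model, where untreated ones would generally count as combined-outcome remitters with no diabetes to remit

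*Protocol article*

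**What the plan says.** The article describes its population in two ways.

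- Abstract, Methods and analysis: "A prospective multicentre observational cohort study of adult patients with T2DM and obesity undergoing Roux-en-Y gastric bypass surgery".
- Methods and analysis, design statement: a study "investigating predictors of diabetes remission in patients with diabetes/pre-diabetes undergoing RYGB surgery".
- Table 1, inclusion criteria: "Patients with pre-diabetes or diabetes eligible for bariatric/metabolic surgery on the NHS".

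The Outcomes section gives the primary outcome in two versions, both assessed at 15 months: complete remission alone, and partial and complete remission together. The stricter category has this rule: "complete remission is fasting glucose <5.6 mmol/L, glycated haemoglobin (HbA1c) <42 mmol/mol on no anti-diabetic agents". The wider category is set out separately in the same sentence: "partial remission is defined as fasting glucose 5.6–6.9 mmol/L, HbA1c <48 mmol/mol on no anti-diabetic agents". Neither requires diabetes at baseline.

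The Predictors section says that the logistic model "will be built using the prospective cohort data". Its Table 3 lists HbA1c, fasting plasma glucose and diabetes duration among the candidate predictors. The area under the ROC curve is the main performance measure. The sample size section plans "to predict a 75% partial and completed diabetes remission rate from multiple predictors" and states that "a sample size of 150 provides 90% power at the two-sided 5% significance level".

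**The concern.** Someone with pre-diabetes has no diabetes to remit. On its ordinary meaning (glycaemia above normal but short of diabetes), pre-diabetes is much the same band that the article calls partial remission. Scored by the article's rule, an untreated pre-diabetic patient is generally a combined-outcome remitter before surgery and stays one unless glycaemia worsens.

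Such patients are easy to recognise from the candidate predictors. Baseline HbA1c and glucose nearly identify them, and diabetes duration has no value for them. A model fitted to the mixture earns part of its discrimination by separating people with diabetes from people without it. The planned bootstrap validation cannot expose this, because each resample carries the same mixture.

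The stated purpose is to prioritise surgery for patients predicted to have remission. An AUC and a remission rate raised by patients without diabetes would mislead on that purpose.

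**Working it through.** **1. Outcome criteria applied at baseline**

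The article does not define pre-diabetes; sub-diabetic glycaemia is assumed here.

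- Untreated, glucose 5.6–6.9 mmol/L and HbA1c below 48 mmol/mol: meets partial remission, so meets the combined outcome. Does not meet complete remission.
- Untreated, HbA1c 42–47 mmol/mol with glucose below 5.6 mmol/L: read literally, meets neither definition.
- On a glucose-lowering agent: meets neither at baseline, because both require no agents.

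The problem is therefore mainly one of the combined outcome in untreated patients.

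**2. The plan's own sample size**

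Inputs from the sample size section: remission p = 0.75, OR 2.0 per SD, R² = 0.10, two-sided 5%, 90% power, 15% loss.

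- n = (1.960 + 1.282)² / [0.75 × 0.25 × (ln 2)²] / (1 − 0.10) = 129.6 evaluable.
- 129.6 / 0.85 = 152.5, so 153 enrolled, against 150 stated.
- With 150 × 0.85 = 127.5 evaluable, power = Φ(√(127.5 × 0.9 × 0.1875) × ln 2 − 1.96) = 89.5%.
- With 100 analysed, the same formula gives 81.3%, matching the stated fallback of more than 80%.

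The plan's arithmetic is reproduced to within 3%.

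**3. Pooled remission rate**

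Let f be the pre-diabetic share. The article gives none; 10% to 30% is an assumed range. Take 75% remission in T2DM and assume that 95% to 100% of pre-diabetic patients are scored as remitters. Then the pooled rate = f × (0.95 to 1.00) + (1 − f) × 0.75. For f = 20%: 0.19 + 0.60 = 0.79, up to 0.20 + 0.60 = 0.80.

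**4. Pooled AUC**

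The AUC is the probability that a randomly chosen remitter ranks above a randomly chosen non-remitter. If all pre-diabetic patients are scored as remitters, every non-remitter has T2DM, and

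pooled AUC = [f × A_pre + (1 − f) × r × A] / [f + (1 − f) × r],

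where r = 0.75 is remission in T2DM, A = 0.70 is the assumed AUC in T2DM, and A_pre is the probability that a pre-diabetic patient ranks above a non-remitter, assumed to be 0.9 to 1.0. For f = 20%:

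- A_pre = 0.9: (0.18 + 0.42) / 0.80 = 0.750.
- A_pre = 1.0: (0.20 + 0.42) / 0.80 = 0.775.

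**5. Power if the model is restricted to T2DM**

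The formula of step 2 is used with n = 127.5 × (1 − f) and 75% remission.

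| Share f | Pooled remission rate | Pooled AUC (T2DM: 0.70) | T2DM evaluable | Power, T2DM only |
|---|---|---|---|---|
| 10% | 77–78% | 0.73–0.74 | 115 | 86% |
| 20% | 79–80% | 0.75–0.78 | 102 | 82% |
| 30% | 81–83% | 0.77–0.81 | 89 | 77% |

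Power depends on the T2DM remission rate. At 70% instead of 75%, it is 86% with 102 patients and 81% with 89.

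**The case against.** The strongest reply is that an article condenses a fuller plan. Eligibility for the cohort is not membership of the primary model, the analysis set may be fixed elsewhere, and pre-diabetic participants are useful for the secondary and mechanistic aims. The Introduction also says that the consensus definition of remission depends on withdrawing T2DM drugs for 1 year, which hardly fits a person who takes none. This shows that the authors may not intend to score pre-diabetic patients as remitters. It does not remove the problem: the article does state the eligible population, the outcome rule and the data for the model, and followed as written they produce that scoring. The design statement itself ties remission to the mixed population, against the abstract.

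Other parts of the reply stand and limit the point:

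- A reader might infer that pre-diabetic patients are in remission at baseline on either version of the outcome. The criteria do not support that, as step 1 of the working shows.
- A reader might infer that the planned 75% is itself inflated, or that the sample size is wrong. The article does not say whether the 75% already includes pre-diabetes, and the calculation reproduces.
- Undefined diabetes duration is a minor matter. Table 3 gives its predictors as examples, and coding belongs in an analysis plan.
- The study is described as preliminary and in need of external validation, which softens the consequence but does not correct the estimate.

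**Conclusion.** The concern holds for the combined outcome. The article contradicts itself on who is studied, and its text as written would put patients with no diabetes to remit into the remission model, generally as remitters if untreated. The complete-remission version is less affected.

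The direction follows from the article's own criteria and predictor list: relative to T2DM patients alone, the remission rate and the AUC go up. The AUC rises only if pre-diabetic patients are ranked higher against non-remitters than T2DM remitters are. That is very likely with HbA1c and glucose as candidates, but if A_pre were also 0.70 there would be no inflation.

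The size is conditional. It rests on an unknown pre-diabetic share and on assumed values for the T2DM AUC and A_pre. Under those assumptions the inflation is about 0.05 to 0.11 at shares of 20% to 30%, up to roughly the ±0.1 precision planned for the AUC. It would be wrong to report any one of these figures as the bias of this study.

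**What to change.** 1. Reconcile the abstract, the design statement and Table 1 on whether the study population is T2DM only or includes pre-diabetes.
2. State that the primary remission model, in both outcome versions, is fitted and validated in participants with T2DM at baseline, and that only they count towards its power.
3. Keep pre-diabetic participants for the secondary and mechanistic aims, and report them separately.
4. Restate power for the T2DM number. Keeping 90% needs about 130 evaluable, or 153 enrolled, patients with T2DM on the plan's own assumptions.

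This is analysis-population wording and needs no new data. The price is a smaller model sample and somewhat lower stated power. Up to a pre-diabetic share of about 20%, the result (102 evaluable, 82%) stays within the fallback that the article already accepts, 100 analysed with more than 80% power. At 30%, with 75% remission, it does not (89 evaluable, 77%).
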